#### Potential outcome measures-proxy (carer) report

The primary outcome measure is the Modified Overt Aggression Scale (MOAS: [43]) measures four types of aggressive challenging behaviour over the past week (verbal, against objects, against self, against others) and measures both severity and frequency. The MOAS has good internal consistency and test-retest reliability (*α* = 0.75) for the rating of aggression. The MOAS will also be administered to the carer by the clinician delivering the intervention on a weekly basis.

Carers will also complete proxy versions of the EQ-5D-Y [48], CHU-9D [50], and ICECAP-A [51] so that their perception of the quality of life of the person they care for can be measured. In addition, the following measures will be utilised.
*The Glasgow Depression Scale-Carer supplement (GDS-CS):* A 16-item scale that asks how often depression symptoms have occurred over the past week [46].
*Anxiety, Depression, and Mood Scale (ADAMS):* As there is no equivalent of the GDS-CS41 for anxiety, the general anxiety scale of the ADAMS will be utilised as a proxy report measure of anxiety [52].
*Client Service Receipt Inventory-European Version (CSRI-EU):* This has been used in previous ID research and examines the participant’s use of medication and health care, social care, day, and community services [53].

#### Qualitative interviews

Qualitative semi-structured one-to-one interviews with participants and carers will be conducted after all outcome data have been collected (6 months after baseline) focusing on the interview topics described below.
*Participants:* How accessible/acceptable SoF meditation was, the impact upon their feelings and expressions of anger, their quality of life, adherence and perceived barriers to the intervention, use of the mindfulness practice audiofiles at home, whether they will continue to use SoF meditation, exploration of any relationship changes with their carer, and any future support needed.
*Carers:* Perceived impact of the intervention on their offspring/client, their relationship with their client/ family member throughout the intervention, and exploring what, if any, impact it had on their own lives, both personally and as a carer.
*UMAA-LD SoF therapists:* their experiences of mindfulness prior to training, their experience of being trained to use UMAA-LD SoF, experiences of delivering the UMAA-LD SoF, including the accessibility of the manual for themselves and clients and the perceived effects on participants and carers.

### Method of analysis

As this is a feasibility study, no hypothesis is to be tested, and no formal analysis of outcome variables will be made as the study is not powered for definitive analysis.

The primary measures of interest are patient recruitment, attrition, and response rate for questionnaires. Feasibility metrics (e.g. recruitment and retention rates, clinical characteristics, duration of the intervention, etc.) will be analysed first, together with adherence outcomes (patient acceptance and adherence to the intervention). The mean change from baseline together with associated variances will be calculated for all measures and will be presented as point estimates together with 95 % confidence intervals. An estimation of the precision of the means and variances will be made to inform the power calculation for the main RCT protocol. Framework analysis [54] is the planned approach to analysing the qualitative interview data.

Initial psychometric properties of the MAIDS will be evaluated using baseline data collection. Internal consistency for the MAIDS total score will be estimated in addition to initial convergent validity (association with baseline mental health measures).

#### Health economic evaluation

To address aim 3, the health economics component of the study will be conducted from a public sector multi-agency perspective [55]. As there is limited evidence of self-reported HRQoL and service use questionnaires being used in an ID population, the principle aim of the health economics evaluation will involve piloting the key outcome measures. A comparison will be made between the participants’ self-reported HRQoL and proxy ratings of HRQoL. Descriptive statistics will be compared with other study outcomes and available social norms. The correlation between study outcome measures will be assessed to explore the construct validity of measures in this population.

The intervention will be costed using micro-costing techniques that have previously been successfully used in costing MBIs and other complex psycho-social interventions [56]. Patterns of health care, social care, and other service use over the preceding four months will be explored and costed using national unit costs [57, 58]. A period of 4 months is sufficient for a representative picture of service use to be gauged, yet recent enough for the respondent to recall accurately the frequency and nature of contacts [59, 60]. As the intervention follow-up period is less than 1 year, it will not be necessary to discount costs [55].

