**Methods/design:**

For this feasibility study, a UK protocol will be developed for use by health professionals within National Health Service (NHS) Intellectual Disability (ID) teams, based upon Singh’s Soles of the Feet manual. Twenty adults with intellectual disabilities and identified problems with anger control will be recruited and six sessions will be delivered by a trained ID clinician. The study will monitor participant’s aggressive behaviour, health-related quality of life, anxiety, depression, and use of support services (medication, hospital appointments etc.). These will be measured at three time points: (1) Baseline (within 2 weeks prior to the first session of the intervention), (2) 2 months post-baseline, and (3) 6 months post-baseline. Qualitative interviews will be conducted with participants, their carers, and the therapists who delivered the intervention. In order to help design an economic evaluation alongside a future full trial, we will cost the intervention and test the acceptability and validity of health economics measures to record resource use and health-related quality of life outcomes.

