### Measures

A researcher is responsible for collecting all feasibility data and outcome measures. The primary aim of these outcome measures is to test the suitability and practicality of the measures with adults with ID. Following the initial screening visit, where capacity to consent is assessed, a baseline visit will be arranged prior to the commencement of the intervention where demographic information on age, gender, and current residential status will be gathered. All of the feasibility outcome measures described below will be taken at the three time points of baseline, 2 months post-baseline, and 6 months post-baseline.

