#### Measures (administered to the participant with ID)

All of the potential outcome measures described below will be taken at the three time points of baseline, 2 months post-baseline, and 6 months post-baseline.

All self-report measures used have been adapted for use with an ID population or have been evaluated by the research team and are likely to be appropriate measures for use with individuals with ID.
*Novaco Anger Scale (NAS):* A 60-item scale exploring how an individual experiences anger, with three subscales: cognitive, arousal, and behavioural, that constitute a total score for anger disposition [44].
*Provocation Inventory (PI):* A 25-item scale that identifies the kinds of situations that induce anger in particular individuals [47].
*The Glasgow Depression Scale for adults with Learning Disabilities (GDS-LD):* A 20-item scale that asks how often depressive symptoms have occurred over the past week [46].
*The Glasgow Anxiety Scale for adults with Intellectual Disabilities (GAS-ID):* A 27-item self-rating scale that assesses how often anxiety symptoms have occurred over the past week [45].
*EQ-5D-Y (Youth version of the EQ-5D generic Health Related Quality of Life questionnaire: HRQoL):* This is a standardised and validated instrument on HRQoL and is intended for use with children and adolescents aged between 7 and 12 years old [48, 49]. There are currently no generic quality of life questionnaires adapted for people with ID.
*CHU-9D (A paediatric generic preference based measure of HRQoL):* This is intended for use with children aged 7–17 years [50]. There are currently no generic quality of life questionnaires adapted for people with ID and challenging behaviour.
*ICECAP-A (ICEpop CAPability measure for Adults):* A measure of capability for the general adult (18+) population for use in economic evaluation [51].

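### At the 2-month visit the four-month service-use recall reaches back two months before baseline, so the 2-month change in service use and cost is diluted

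*Protocol article*

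**What the plan says.** Under Health economic evaluation, the article sets one recall period for service use: "Patterns of health care, social care, and other service use over the preceding four months will be explored and costed using national unit costs". It defends the length on representativeness, saying that "A period of 4 months is sufficient for a representative picture of service use to be gauged", and on accuracy of recall. It does not mention the spacing of the visits.

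The instrument is the CSRI-EU, completed by the carer, which "examines the participant’s use of medication and health care, social care, day, and community services". It is listed under Potential outcome measures-proxy (carer) report. The schedule for that class of measure reads: "All of the potential outcome measures described below will be taken at the three time points of baseline, 2 months post-baseline, and 6 months post-baseline". That sentence stands under Measures (administered to the participant with ID). The Measures section says the same of the feasibility outcome measures, and the abstract names use of support services among the things measured at the three time points.

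The Design section treats the 2-month visit as the measurement directly after the intervention. Method of analysis plans the mean change from baseline, with variances and 95% confidence intervals, for all measures. It also uses the precision of means and variances to inform the power calculation for the later RCT.

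**The concern.** A retrospective service-use form should cover the time since the previous form, or at least should not reach behind the point from which change is measured. Four months does this at the 6-month visit. It does not at the 2-month visit, where only two months have passed since baseline.

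At stake is what the 2-month service-use record means. It is presented as a post-intervention measurement, but it would be partly a second report of the baseline period. Its change from baseline would be too small and its variance would not be that of a true before-after comparison. If service cost is correlated with the other outcomes at that visit to explore construct validity, a figure that reaches behind baseline would stand beside scales that ask about the past week. The third aim includes evaluating the health economic outcomes for a later full evaluation, so the recall period is part of what is being piloted.

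**Working it through.** **Inputs.** Recall length 4 months (Health economic evaluation). Visits at months 0, 2 and 6 (Measures). First session 0 to 14 days after baseline (Procedure). Six weekly sessions, so 35 days from first to last (Design).

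**The plan's own figure.** The only stated figure is the four-month recall. It equals the gap between the last two visits (6 - 2 = 4), so it fits the 6-month visit exactly. The gap before the 2-month visit is 2 - 0 = 2 months.

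**Windows.** The window at visit t is [t - 4, t].

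| Visit | Window (months) | Before baseline | Overlap with previous window |
|---|---|---|---|
| Baseline | -4 to 0 | 4 of 4 | none |
| 2 months | -2 to +2 | 2 of 4 (50%) | 2 months |
| 6 months | +2 to +6 | 0 of 4 | 0 months |

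Across the two follow-up windows, 2 of 8 recalled months (25%) precede baseline.

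**Relation to the sessions** (30.4375 days per month, so 2 months = 60.9 days and 4 months = 121.75 days).
- Share of the 2-month window before the first session: 60.9/121.75 = 50% to (60.9 + 14)/121.75 = 61%.
- Share after the last session, which falls on day 35 to day 49: (60.9 - 35)/121.75 = 21% to (60.9 - 49)/121.75 = 10%.

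**Effect on the change from baseline.** Assume a constant monthly cost c before baseline and c(1 - x) after it. The monthly mean over the 2-month window is (2c + 2c(1 - x))/4 = c(1 - x/2). The apparent change is -x/2.

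| True fall x | Apparent fall at 2 months |
|---|---|
| 10% | 5% |
| 20% | 10% |
| 40% | 20% |

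**Effect on the variance.** As an illustration, let a person's monthly costs vary independently around that person's own level with variance s². Stable differences between people cancel in a change score.
- Overlapping windows: the two shared months cancel, leaving two months against two. Variance of the four-month change is 4s², or 4s²/16 = 0.25s² per month.
- Two separate four-month windows: 8s², or 8s²/16 = 0.50s² per month. The overlap therefore halves the variance.
- Two months since baseline against four months before: s²/2 + s²/4 = 0.75s² per month.

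The last line shows the price of a shorter window. Even so, the ratio of expected change to its standard deviation is (x/2)/(0.50s) = 1.00x/s with the overlap and x/(0.87s) = 1.15x/s without it, with x here in the same cost units as s. The smaller variance of the overlapping version is not a gain in information.

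**The case against.** The strongest reply is that little rests on this figure. Method of analysis tests no hypothesis and names recruitment, attrition and questionnaire response as the primary measures. The three progression criteria, under Protocol for a full-scale effectiveness trial, concern recruitment, retention and adherence. The economic work mainly pilots instruments, and the intervention's own cost is obtained separately by micro-costing. A clean comparison remains between baseline and 6 months, with equal four-month windows. All of this stands and limits the weight of the point.

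A second reply is that the article condenses a fuller protocol, and the form used at 2 months may carry its own wording. That is possible, and it lowers certainty about what carers will be asked. But the article is not silent: it fixes a length, gives reasons for it, and makes no exception by visit.

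A third reply is that a two-month window is less representative and still falls largely within the delivery period. Both parts are true: of about 61 days, only some 12 to 26 follow the last session. The shorter window removes the pre-baseline time. It does not turn the 2-month record into a purely post-treatment one.

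A reader might also infer that follow-up costs are double-counted, with eight recalled months standing for six (8/6 = 1.33, or 33% too much). This would follow only if the visit costs were added together, and the article nowhere says that they will be. Nor does the text support the claim that the fault will pass into the RCT: that protocol is to be written later, and no recall period for it is fixed here.

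**Conclusion.** The point holds for the 2-month visit only. As written, the recall there spans months -2 to +2, shares two months with the baseline record, and spends half of its time before baseline. The planned 2-month change from baseline in service use and cost is therefore diluted, and its variance is distorted by the shared months.

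The overlap and the 50% share follow directly from the stated recall and schedule. Dilution by half rests on constant monthly cost with a step change at baseline; a gradual or later change would give a different factor. The halved variance rests on independent monthly costs of equal variance.

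It would be too strong to say that half of all post-intervention cost is pre-intervention. Half is a share of recall time at one visit, equals half of cost only if monthly cost is constant, and becomes 25% across both follow-up windows. Severity is moderate: the measure being piloted is affected, but no primary feasibility result or progression decision is.

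**What to change.** Keep four months at baseline and at 6 months. At the 2-month visit, ask the carer about use since the baseline visit. The windows become -4 to 0, 0 to 2 and 2 to 6 months, with no overlap and no gap. Express service use and cost per month before calculating change from baseline, because the windows then differ in length. If a follow-up total is reported, sum only the 0-2 and 2-6 month windows.

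The cost is one changed recall instruction on the 2-month form and one sentence in the analysis. Carers have a shorter period to remember. The downside is that two months capture fewer contacts in 20 participants, so the 2-month monthly rate is less precise. The change should be made before data collection, since a single four-month answer cannot reliably be split afterwards. If the 2-month form already asks only about use since baseline, it is enough for the protocol to say so.

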#### Protocol for a full-scale effectiveness trial

To address aim 4, a full study would be considered feasible if (1) recruitment rate found was more than 50 %, (2) if the retention rate found was more than 50 % at final follow-up, and (3) if adherence rate was greater than 50 % for the completing participants.

### Ethics and consent

Ethical approval has been received from both Bangor University, and the NHS Research Ethics Committee (ref 15/WA/0213), and the study is registered with the UK Clinical Research Network Study portfolio—database no. 16743. Our protocol around assessing capacity to consent has been designed in accordance with the Mental Capacity Act [61] and ID best practice [62]. We will use developmentally appropriate information sheets and consent forms. It will be made clear to participants that they have the right to withdraw from the study at any time. Those unable to consent and those who do not consent will continue to receive treatment as usual from their service. Consent will be sought from carers separately.

## Discussion

The prevalence of aggressive behaviours among people with ID is further accentuated by limited access to evidence-based interventions. Leading ID researchers have called for creative and more effective interventions for anger [16].

Research in the field of ID shows the negative impact of challenging behaviour resulting from anger that can lead to a lower quality of life, a negative impact on carer well-being, reduced access to community services and admission to intensive and specialist, and therefore costly, residential, or forensic services [3, 9–11]. Therefore, within specialist ID NHS services and mainstream mental health services, there is a need to further develop clinical practice to support adults with ID with mental health problems, including anger and aggressive behaviour. There has been some work to adapt and evaluate CBT methods for anger (although few examples of high-quality research), but little focus on adapting other psychological therapies from mainstream services.

This feasibility study will examine an evidence-based intervention for anger in adults with ID and is anticipated to benefit participants directly by offering a valuable treatment approach where limited approaches exist currently. An intervention informed by mindfulness may also have other benefits with an ID population because it encourages the individual to develop an attitude of shared responsibility for their own mental health with consistent practice of self-management skills. Thus, the proposed UMAA-LD SoF intervention is potentially useful both as an early intervention measure for reduction in aggressive behaviour and also as a strategy for long-term management of anger and aggressive behaviour. Mindfulness training is also non-intrusive, an alternative to medication and promotes resilience and well-being. By developing familiarity with mindfulness and basic meditation techniques, adults with ID may also be better placed to access mainstream mindfulness classes. Adults with ID may (perhaps with the support of their carer) be empowered to manage other emotional problems (e.g. anxiety) using their new transferable mindfulness skills. Finally, reducing anger and associated challenging behaviour may contribute towards participants’ ability to engage with paid employment, improving their economic situation and providing meaningful activity.

In health economics evaluations, the NHS traditionally prefers a cost-utility approach to economic analysis, whilst in Public Health cost-benefit and cost-consequence analysis are considered to be more appropriate by NICE [63]. The UMAA-LD SoF intervention may result in benefits and possible cost savings that goes beyond the health service; therefore, a public sector multi-agency approach to economic analysis is likely to capture this wider potential impact of the intervention.

There will likely be variability in therapists’ previous experience of practicing or teaching mindfulness-based approaches. The UK Good Practice Guidelines for teachers of mindfulness-based programmes such as MBSR and MBCT stipulate that those delivering MBIs have personal experience of mindfulness practice [64]. However, due to practicalities of recruiting ID health professionals to deliver UMAA-LD SoF, we will aim for this but anticipate this will not always be possible. Those who do not have personal experience of mindfulness practice in advance will be offered support and encouragement to develop this. Although this intervention is mindfulness informed, it is not mindfulness-based, because it does not comply with UK good practice guidelines (although these were developed for teachers of the 8-week courses for the general public or clinical populations and are not intended to be specific for ID populations [64]). This aspect of the project will be closely monitored as part of the feasibility study, through the qualitative interviews with the therapists, as the personal practice of the teacher and how this is embodied could be important with an ID populations as it bypasses cognitive verbal channels.

We anticipate that the qualitative information will enhance the quantitative analysis and RCT protocol. Although preliminary data on the effectiveness of the intervention will be taken, it will not give insight into the mechanisms of change. This question will be explored in the qualitative data, with participants, their carers, and with clinicians. The qualitative data will also help identify any practical barriers or facilitators to participating in the intervention and any unanticipated positive or negative affects of the intervention.

Successful anger management intervention trials using RCT have been utilised for people with ID [38] allaying concerns expressed by some researchers about whether it is feasible to undertake RCT’s with people with ID [65]. This feasibility study will examine whether UMAA-LD SoF may be suitable for investigation as a large-scale RCT. First, all data collected will be used to make any final revisions to the UMAA-LD SoF protocol, if necessary. Secondly, if the feasibility study is promising, an intervention package and protocol for an RCT with concurrent economic evaluation will be developed. The intervention package will include a validated UMAA-LD SoF manual, a new mindfulness measure with initial psychometric data (MAIDS), a complete description of the intervention, clinician training method, method to measure treatment fidelity, and follow-up procedures. The protocol will draw on pilot data for recruitment pathways and inclusion and exclusion criteria. It will provide valuable information into the feasibility of key issues such as recruitment and acceptability of the UMAA-LD SoF protocol with participants, carers, and clinicians.
